Considering that the endogenous production of NO is reduced with aging [13], it was recently confirmed that the hypotensive effects caused by beetroot juice are more evident in older adults (50 to 70 years of age) when compared to a young population (18 to 30 years of age) [14]. In addition, a meta-analysis recently published by our group showed that in patients with SAH, NO3-rich beetroot juice supplementation was able to reduce systolic blood pressure by − 4.95 mmHg (95% CI: − 8.88; − 1.01) without significant differences to diastolic blood pressure [10].

Accordingly, physical exercise is considered one of the non-drug therapeutic strategies that directly helps to reduce blood pressure levels by causing post-exercise hypotension (PEH) [15] and contributing to increased baroreflex sensitivity [16]. HPE has excellent clinical value for hypertensive patients, as it can be used as a strategy to reduce blood pressure levels both acutely and chronically. Aerobic exercise is considered one of the most efficient to generate PEH [17–19].

In conjunction with heart rate (HR) and blood pressure (BP) levels, heart rate variability (HRV) has been used as a non-invasive and independent metric for assessing cardiovascular risk [11, 20, 21]. Through the adjacent intervals between consecutive heartbeats (RRi), it is possible to analyze the behavior of autonomic efferents (parasympathetic and sympathetic) on the heart [22, 23]. Part of the effects caused by hypertension on cardiac activity involves adjustments in the autonomic nervous system (ANS), and therefore, in hypertensive patients, there is a decrease in HRV at rest [24], and after exercise, there is a delay in recovery of parasympathetic modulation [25]. These two factors are evidence of autonomic dysfunction and cardiovascular inadaptability that certainly contribute to the emergence of disorders and adverse cardiovascular events [26] and a risk factor for overall mortality [27]. In SAH, endothelial dysfunction is documented in the macro- and microcirculation of the coronary, peripheral, and renal circulation. These effects are mainly caused by decreased endogenous nitric oxide production through increased oxidative stress and endothelial damage caused by increased blood shear force [28].

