
#### Exercise variables

On the first day, the collections will occur after the participants ingested 140 mL of beet juice (with or without nitrate). The seventh day of beet juice ingestion (70 mL) (with or without nitrate) will also be collected. On the collection days (first and seventh days of intervention), the variables will be obtained at the following times (Fig. 1):

I)Rest phase (zero to 135th min): After drinking the juice, the participants will remain at an initial rest in a sitting position. Then, 30 min before starting the measurements, the participants will be instructed to empty their bladders. Upon returning to the room, a recording strap (Polar® H10) will be placed on the chest, in the region of the distal third of the sternum, to record beat-to-beat HR throughout the collection, mediated by a heart rate monitor (Polar® RS800CX, Finland). Then, the participants will be placed on a stretcher in the supine position and will remain at rest. After the remaining time, HR values will be recorded (120th minute), HRV recording (120th to 125th min), systolic blood pressure (SBP) (125th minute), diastolic blood pressure (DBP) (125th minute), blood collection (15mL) (125th min), and analysis of endothelial function (flow-mediated dilation) (125th to 135th min).II)Physical exercise (135th to 175th min): Participants will perform the physical exercise for 40 min on a treadmill at a speed corresponding to 65–70% of VO2peak [29]. In this phase, the highest HR value reached during the exercise will be recorded, and the HRV recording will also be carried out in the last 5 min (35th–40th min).III)Recovery phase (175th to 235th min): At the end of the activity, the participants will be placed in the supine position again and will be monitored for another 60 min, recording their HR at 30 s, 60 s, 120 s, 180 s, and 300 s. Blood collection (15 mL) will be performed between 5 and 10 min after exercise. HRV will be recorded after exercise at the following times: 0–5 min, 10–15 min, 20–25 min, 30–35 min, and 40–45 min. SBP and DBP will be recorded after exercise at the 45th minute and 60th minute post-exercise. To avoid errors in the measurements of the evaluated parameters, a single evaluator will perform these measurements throughout the experiment. The flow-mediated dilation technique to assess endothelial function will be employed after exercise during the 50th–60th minute post-exercise interval.

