### Primary outcomes

#### Blood pressure

The measurement of systolic and diastolic blood pressure will be performed indirectly using a digital sphygmomanometer (OMRON M2, Model HEM-7121-E, Jundiaí, São Paulo, Brazil) previously calibrated on the participants’ left arm.

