### Statistical methods

For data analysis, descriptive statistics will be performed to characterize the sample. The results will be presented with mean and standard deviation values when the residual values of the variables present normal. Values in the median distribution and interquartile intervals will be presented when the residuals’ assumptions of normality and homoscedasticity are not reached. Data will be analyzed using linear analysis of mixed effects adjusted for age, drugs, and VO2peak, considering time and treatment as an independent variable. Per-protocol analysis will be performed to account for possible dropouts during the study. The analysis will be conducted according to the intention-to-treat principle. The generalized mixed linear model will treat the missing values, using maximum likelihood to estimate the model parameters. Differences in all tests will be considered significant when the *p* value is less than 0.05. The statistical program used will be RStudio (v. 1.0.136). The confidence interval at the 95% level will be exposed when we describe the comparison values of the variables with each other. The magnitude of significant differences will be quantified through effect size calculated using Cohen’s *d*. A large effect size will be considered for values greater than 0.9 and a medium effect size for values between 0.9 and 0.5 [54].

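### Systolic and diastolic pressure are both primary, with 12 possible nitrate-placebo contrasts, none of them designated and 0.05 applied to every test, so the error rate of the primary claim is above 5%

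*Protocol article*

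**What the plan says.** Under the plural heading Primary outcomes, the article has one entry, Blood pressure: "The measurement of systolic and diastolic blood pressure will be performed indirectly using a digital sphygmomanometer". It ranks neither pressure above the other and names no day or time.

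The section Exercise variables sets the schedule. For days: "On the collection days (first and seventh days of intervention), the variables will be obtained at the following times". At rest: "systolic blood pressure (SBP) (125th minute), diastolic blood pressure (DBP) (125th minute". After exercise: "SBP and DBP will be recorded after exercise at the 45th minute and 60th minute post-exercise".

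The Statistical methods specify a linear mixed model, "considering time and treatment as an independent variable". The decision rule is "Differences in all tests will be considered significant when the" p value is under 0.05. No primary contrast, testing order or adjustment accompanies it.

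Two other places bear on the choice of primary variable. The Sample size section plans on a single 5 mmHg reduction. The Background and rationale cites a meta-analysis in hypertensive patients with an SBP reduction of 4.95 mmHg, "without significant differences to diastolic blood pressure".

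**The concern.** The trial has two stated hypotheses, acute and 1-week, but its primary outcome is an unranked set of readings and its decision rule treats every test alike. The hypothesis itself speaks only of improved cardiovascular parameters. A report could therefore present any one of several blood-pressure contrasts as the primary finding and still be consistent with the published plan. The stated 5% would then be the error rate of a single test and not of the trial's conclusion.

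DBP adds to the number of tests without a planning basis in the article. The 5 mmHg in the Sample size section appears to be the rounded SBP effect from the Background, and the same source found no significant DBP effect.

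**Working it through.** **1. The plan's own figure.** Inputs from the Sample size section: difference 5 mmHg, variation 4 mmHg (read as a standard deviation), two-sided 5%, power 80%. The two-mean normal formula gives n = 2 x (1.960 + 0.842)^2 x (4/5)^2 = 10.05, rounded up to 11. This reproduces the stated minimum of 11. The calculation covers one comparison at 0.05.

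**2. The number of contrasts.** 2 pressures x 3 times (125 min rest, 45 and 60 min post-exercise) x 2 days = 12 possible nitrate-placebo contrasts. The article does not say how many will be tested, so four counts are carried:
- 2 tests: one treatment effect per pressure;
- 4 tests: one per pressure per day;
- 6 tests: one pressure at all times and days;
- 12 tests: every contrast.

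**3. Chance of at least one p<0.05 if nitrate has no effect.** For k independent tests this is 1 - 0.95^k. For correlated tests it was simulated with two-sided normal tests sharing a common correlation. The article gives no correlations, so those below are assumptions.

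| Tests | independent | 0.3 | 0.5 | 0.7 | 0.9 |
|---|---|---|---|---|---|
| 2 | 9.8% | 9.5% | 9.1% | 8.3% | 7.0% |
| 4 | 18.5% | 17.4% | 15.6% | 13.0% | 9.4% |
| 6 | 26.5% | 24.2% | 20.7% | 16.4% | 10.9% |
| 12 | 46.0% | 39.8% | 32.0% | 23.2% | 13.5% |

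Paired t-tests with 16 participants (the recruitment figure in the Sample size section) give nearly the same for 12 tests: 33% at correlation 0.5 and 14.5% at 0.9. Letting the correlation differ between pressures, times and days gave 25% to 43% over the combinations tried.

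**4. What the row for 6 tests shows.** Making SBP the only primary outcome does not suffice by itself. If all six SBP contrasts stay open, the chance is still 11% to 26%, so the contrast has to be named as well.

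**5. Power cost of a 0.025 threshold.** With the formula and inputs of step 1, n rises from 11 to 13 (12.17 rounded up). At n = 16, power falls from 94% to 90%; at n = 11, from 83% to 75%. With Holm these are the less favourable figures, because the second contrast is tested at 0.05 once the first has succeeded.

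**The case against.** The strongest objection is that the 12 contrasts come from the measurement schedule and not from the analysis section. The Statistical methods describe a mixed model with time and treatment. One treatment effect or treatment-by-time test per pressure fits that text as well as 12 pairwise comparisons do. This stands. The 12-test figures are therefore conditional, and the 2-test and 4-test rows belong beside them. Even the 2-test row lies above 5%.

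Second, the article has no rule that one significant reading makes the trial positive. The hypothesis refers to benefit both acutely and over one week, which could be read as requiring both. This also stands: the inflation applies if any one significant contrast may carry the claim. The article does not exclude that use, and it does not state it either.

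Third, the choice of contrast and the multiplicity procedure are often left to an analysis plan, which is not shown. Silence on them would be no finding. Here, however, the article positively sets 0.05 for all tests and positively makes both pressures primary. An analysis plan that controlled the error would have to depart from that text.

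Fourth, the Sample size section does not say that its 5 mmHg is systolic. That is an inference from the matching meta-analysis figure, though a reasonable one.

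A reader might also infer that a positive primary result has about a one-in-three chance of being false. The documents do not support this. The one-in-three figure is the probability of some significant result given no effect, at an assumed correlation near 0.5. The probability of no effect given a significant result also needs power and a prior. With 33% for the former and 80% power, it is 62%, 29% or 9% for a prior chance of a real effect of 20%, 50% or 80%.

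**Conclusion.** The point holds in this form: two primary pressures, up to 12 contrasts, no designated primary test, and an unadjusted 0.05 for every test. If nitrate had no effect and any significant contrast could be claimed, the chance of at least one would be about 14% to 46% with all 12 tested, 9% to 19% with 4, and 7% to 10% with 2, for common correlations from 0.9 down to 0. The upper ends follow from arithmetic alone; the rest depends on correlations that the article does not give. No single figure in these ranges can be called the trial's error rate, because the article fixes neither the number of tests nor the rule for success. That openness is itself the defect. It should be closed before unblinding, since a contrast chosen after the results are known cannot be made confirmatory.

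**What to change.** In Primary outcomes and Statistical methods:

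- Make SBP the only primary outcome, in line with the apparent basis of the sample size.
- Name one nitrate-minus-placebo contrast from the mixed model for each stated hypothesis: acute (day 1) and 1-week (day 7).
- Have the sponsor choose, before unblinding, whether that contrast is the resting reading, the post-exercise readings or an average. Averaging rest with recovery is debatable, because the Objectives treat resting and exercise conditions separately.
- Apply Holm across the two contrasts: the smaller p value against 0.025 and, if that succeeds, the larger against 0.05.
- Report DBP and the remaining SBP readings as secondary, with confidence intervals and no confirmatory claim.

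This holds the chance of any false primary claim to at most 5%.

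The costs are moderate. DBP and the other readings lose confirmatory status. Power for the first contrast to succeed is slightly lower than for the single comparison in the Sample size section (step 5 of the working). No visit or measurement changes, but the article's own rules require ethics review and a registry update. Recruitment was expected to finish around January 31, 2023, so the amendment would come late. It remains valid as long as the allocation codes are closed, and the blinding section keeps them closed until the analysis is done.

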### Sample size

The number of participants in this study considered the most recent meta-analysis study, which found a reduction of 5 mmHg caused by beetroot juice rich in nitrate in patients with SAH as significant with a variation of 4 mmHg [10, 11]. We applied these values in the Hedwig Harvard Sample Calculator software online, considering a bilateral 95% confidence interval and a power analysis of 80% that provided a minimum of 11 participants for this clinical trial [29]. We will recruit sixteen postmenopausal women diagnosed with SAH to ensure a sufficient sample size after the interventions. This sample size is consistent with previous studies that investigated the effects of BRJ on BP in patients with SAH. The Amaral et al. [29] study used 13 postmenopausal women to examine the impact of BRJ on PEH. Broxterman et al. conducted two studies in patients with SAH medicated and non-medicated. In both trials, the sample was 13 and 14, respectively. The most recent investigation in this field conducted by Siervo et al. [53] used 16 patients with SAH.

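### Cohen's d is planned for significant differences, so the reported d values and their labels will be inflated where the true effect is small or moderate

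*Protocol article*

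**What the plan says.** All of the reporting rules are in Statistical methods:

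- **Significance:** "Differences in all tests will be considered significant when the *p* value is less than 0.05".
- **Effect size:** "The magnitude of significant differences will be quantified through effect size", with Cohen's d as the measure. The section does not say which SD forms the denominator.
- **Labels:** "A large effect size will be considered for values greater than 0.9 and a medium effect size for values between 0.9 and 0.5". Values below 0.5 have no label.
- **Model:** a linear mixed-effects model with treatment and time, adjusted for age, drugs and VO2peak.
- **Intervals:** 95% confidence intervals accompany comparisons. That sentence is not limited to significant results.

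The number of women differs between sections. Sample size states: "We will recruit sixteen postmenopausal women diagnosed with SAH to ensure a sufficient sample size after the interventions". The allocation section also gives 16, but the abstract gives 25.

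**The concern.** A comparison that reaches p<0.05 in a small sample has, on average, an observed effect larger than the true one. If d is attached to those comparisons and no others, the set of reported d values is biased upwards, and so are the labels.

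The trial has many outcomes to which this applies. The blood-test sections list 24 markers: nitrite, MDA and FRAP (3), metabolic markers (5), inflammatory, vascular and cardiac markers (11), catecholamines (2) and mitochondrial markers (3). Each collection day adds three blood-pressure time points and seven heart-rate-variability windows. The sample size was set for a 5 mmHg change in blood pressure alone, so small or moderate true effects are plausible among the other outcomes. Readers use d to compare outcomes measured in different units, and here they would see it only for the selected ones. An outcome that missed significance would have no standardised magnitude at all.

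**Working it through.** **Inputs from the protocol article.** Two-sided alpha 0.05; n = 11 (stated minimum), 16 (Sample size and allocation sections) or 25 (abstract); two-period crossover, so each woman is her own control; label cut-offs 0.5 and 0.9.

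**Assumptions.** A simple paired comparison with normally distributed differences, and d standardised by the SD of the differences (written d_z). The within-woman correlation r is not given in the article, so it is varied.

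**Step 1: the plan's own figure.** The plan uses a 5 mmHg reduction with a variation of 4 mmHg. Reading 4 as a within-patient SD:

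n = 2 × (1.960 + 0.842)² × (4/5)² = 2 × 7.849 × 0.64 = 10.05, rounded up to 11.

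This matches the stated minimum of 11. On this reading the planned effect is d_z = 5/(4 × √2) = 0.88. If 4 is instead the SD of the paired differences, d_z = 5/4 = 1.25, but the normal formula then gives n = 6, which does not match.

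**Step 2: smallest d_z that can be significant.** Minimum d_z = t(0.975, n−1)/√n.

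- n=11: 2.228/3.317 = 0.67
- n=16: 2.131/4 = 0.53
- n=25: 2.064/5 = 0.41

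The minimum falls below 0.5 from n=18.

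**Step 3: mean reported d_z.** From 100,000 simulated paired trials per setting, averaging the absolute d_z among those with p<0.05:

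| True d_z | n=16: power | n=16: mean reported | ratio | n=25: power | n=25: mean reported | ratio |
|---|---|---|---|---|---|---|
| 0.2 | 12% | 0.69 | 3.4 | 16% | 0.54 | 2.7 |
| 0.3 | 20% | 0.71 | 2.4 | 30% | 0.56 | 1.9 |
| 0.5 | 47% | 0.77 | 1.5 | 67% | 0.63 | 1.3 |
| 0.8 | 85% | 0.92 | 1.15 | 97% | 0.84 | 1.05 |
| 1.25 | 99.6% | 1.32 | 1.05 | 100% | 1.29 | 1.03 |

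**Step 4: the same trials without selection.** If d_z is reported for every trial at n=16, its mean is 0.32 for a true 0.3, 0.53 for a true 0.5 and 0.84 for a true 0.8. The remaining excess of about 5% is the ordinary small-sample bias of d. At a true 1.25 the mean is 1.32 with or without selection, so selection adds almost nothing there.

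**Step 5: a raw-SD standardiser.** On that scale the minimum is d_z × √(2(1−r)). At n=16:

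- r=0.5: 0.53
- r=0.6: 0.48
- r=0.7: 0.41
- r=0.8: 0.34
- r=0.9: 0.24

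It equals 0.5 at r = 1 − (0.5/0.533)²/2 = 0.56. At n=25 the crossing is at about r = 0.27. Inflation remains but is smaller. At n=16 with a true raw-SD d of 0.3, the mean reported value is 0.53 for r=0.7, 0.46 for r=0.8 and 0.37 for r=0.9 (ratios 1.8, 1.5 and 1.2; 50,000 trials each).

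**The case against.** The strongest reply is that d is a supplementary statistic. The model, its estimates, the primary test and the sample size do not depend on it. Descriptive summaries and 95% confidence intervals are promised without restriction to significant results, and for blood pressure a difference in mmHg with its interval is the natural measure. This stands. It limits the harm to the d values and their labels, but it does not remove the selection from them.

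Second, the inflation is modest where the trial is well powered. At the planned blood-pressure effect (d_z of 0.88 or 1.25, depending on how the 4 mmHg is read) it is about 15% or less at n=16. This also stands. The large ratios belong to small and moderate effects.

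Third, the article never uses the word *only*, and an analysis plan that is not shown could add d for other comparisons. That is possible, but the sentence as written ties d to significance. The criticism is of that stated rule, not of a missing detail.

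A reader might go further and infer that every reported d must be at least medium, because 0.53 lies inside the band described as "a medium effect size for values between 0.9 and 0.5". The documents do not support this. It needs 17 or fewer women, a simple paired test and d standardised by the SD of the differences. The article gives both 16 and 25 women, plans a mixed model whose significance threshold need not equal the paired one, and names no standardiser. With a raw-SD d at n=16 and r=0.8, 67% of significant results for a true d of 0.3 fell below 0.5.

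Nor does it follow that the paper would show only inflated magnitudes, given the planned confidence intervals.

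**Conclusion.** The point holds as a reporting bias. Tying Cohen's d to p<0.05 inflates the reported values where the true effect is small or moderate. Under the paired, SD-of-differences assumption, the average overstatement is about 2.4-fold (n=16) or 1.9-fold (n=25) for a true d of 0.3, and about 1.5-fold or 1.3-fold for a true d of 0.5. It is 15% or less from 0.8 upwards. With a raw-SD standardiser the direction is the same and the size smaller, depending on a correlation that the article does not give.

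The unnamed standardiser matters in its own right. At n=16 a just-significant difference is 0.53 on one scale and 0.34 on the other if r=0.8, so its label depends on a choice that the plan leaves open. The primary test and the raw-scale estimates are not affected.

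**What to change.** Replace the effect-size sentence in Statistical methods with: *Cohen's d with its 95% confidence interval will be reported for every planned beetroot-versus-placebo comparison, whatever its p value, using one named standardiser.* State whether that standardiser is the SD of the paired differences, the raw SD or a model-based SD.

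The cost is one sentence and a few more table cells. No new data are needed, and the model and sample size stay as they are.

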### Oversight and monitoring

#### Composition of the coordinating center and trial steering committee

The lead researcher will coordinate the study site. The study will be led by principal investigators. No additional steering committees are considered for this study. The other researchers will participate in regular (monthly) and extraordinary meetings (when necessary) to discuss the progress of the research and possible unforeseen events. We will have two specific researchers available all the time to ensure the participants’ security and that all adverse events, symptoms, and feelings will be reported in this clinical trial. This Trial Committee will be available to participants day-to-day report your symptoms. Furthermore, they will provide further health assistance and guidance to participants searching the health system if necessary.

